## Abstract

**Background:**

Routine oral examination (ROE) refers to periodic monitoring of the general and oral health status of patients. In most developed Western countries a decreasing prevalence of oral diseases underpins the need for a more individualised approach in assigning individualised recall intervals for regular attendees instead of systematic fixed intervals. From a quality-of-care perspective, the effectiveness of the widespread prophylactic removal of mandibular impacted asymptomatic third molars (MIM) in adolescents and adults is also questionable. Data on the effectiveness of appropriate interventions to tackle such problems, and for promoting continuing professional development in oral health care are rare.

**Methods/design:**

This study is a cluster randomised controlled trial with groups of GDPs as the unit of randomisation. The aim is to determine the effectiveness and efficiency of small group quality improvement on professional decision-making of general dental practitioners (GDPs) in daily practice. Six peer groups ('IQual-groups') shall be randomised either to the intervention arm I or arm II. Groups of GDPs allocated to either of these arms act as each other's control group. An IQual peer group consists of eight to ten GDPs who meet in monthly structured sessions scheduled for discussion on practice-related topics. GDPs in both trial arms receive recently developed evidence-based clinical practice guidelines (CPG) on ROE or MIM. The implementation strategy consists of one interactive IQual group meeting of two to three hours. In addition, both groups of GDPs receive feedback on personal and group characteristics, and are invited to make use of web-based patient risk vignettes for further individual training on risk assessment policy. Reminders (flow charts) will be sent by mail several weeks after the meeting.

The main outcome measure for the ROE intervention arm is the use and appropriateness of individualised risk assessment in assigning recall intervals, and for the MIM-intervention group the use and appropriateness of individualised mandibular impacted third molar risk management. Both groups act as each other's control. Pre-intervention data will be collected in study months one through three. Post-intervention data collection will be performed after nine months.

## Background

Routine oral examination (ROE) refers to periodic monitoring of the general and oral health status of patients. The main purpose of ROEs is to prevent the onset of oral diseases and/or prevent further progression. This allows the introduction of preventive interventions at the appropriate time, and reduces the need for operative interventions. In most developed Western countries, a decreasing prevalence of oral diseases underpins the need for a more individualised approach in assigning individualised recall intervals for regular attendees instead of systematic decision-making of fixed intervals. In The Netherlands, about 80% of the population regularly visits the dentist for a check-up about every six months [1]. This implies that many healthy individuals are scheduled for routine oral screening. In 2000, 50% of the Dutch GDPs assigned all their regular patients for ROE twice a year [2], irrespective of level of risk for oral disease. The efficiency of this systematic monitoring system is still disputed in The Netherlands, as well as internationally [3-10]. Recently, two systematic reviews [11,12] and a clinical practice guideline (CPG) advocated an individualised risk-based assessment strategy, given the lack of good scientific evidence [13]. In addition to the debate over the frequency of ROE, GDPs also question from a quality-of-care perspective the effectiveness of the widespread prophylactic removal of mandibular impacted asymptomatic third molars (MIM) in adolescents and adults [14-16].

Recent implementation studies in medical care indicate that evidence on the effect of single interventions is mixed [18,19]. It is as yet unclear how quality of oral care in dental practice can be improved. Research data on effectiveness of interventions to promote continuing professional development for dentists are rare [17]. A previous study showed that small group education sessions did not change dentists' clinical behaviour [20]. The aim of the present study is to evaluate whether a multifaceted strategy can enhance oral health care according to evidence-based dental practice. Consensus-based CPGs on ROEs [13] and on the management of MIMs [20] are available for educational purposes in clinical practice.

### Aim of the study

To determine the effectiveness and efficiency of small group quality improvement on professional decision-making of general dental practitioners (GDPs) concerning risk assessment in ROEs (including assigned recall intervals) and risk management of MIMs for patients (children and adults) in dental practice.

### Scientific hypothesis

Multifaceted implementation of consensus-based clinical practice guidelines (CPGs) for GDPs on ROEs and the management of MIMs in daily dental practice is more effective and efficient compared to dissemination of CPGs only.

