## Methods

### Study design

The study is a cluster-randomised trial with incomplete block design. In one trial arm, the intervention focuses on individual decision-making in scheduling ROEs. In the second arm, the intervention focuses on monitoring and decision-making regarding prophylactic removal versus retention of MIM. Groups of GDPs allocated to either of these arms act as each other's control group. To reduce potential contamination, groups of GDPs are randomised rather than individual GDPs (Table 1). We assumed that the two clinical conditions (or practices) were largely independent of one another, i.e. performing one would not necessarily influence the other. In the ROE arm, the CPG only mentions the necessity of third molars screening in general as routine oral care. In the MIM arm, the CPG provides an extensive, but specific, decision-making algorithm, i.e. how to deal with mandibular asymptomatic impacted third molars.

**Table 1 T1:** Balanced incomplete block design

**Intervention**	**CPG**	
	**ROE**	**MIM**

Group I (ROE)	Intervention	Control
Group II (MIM)	Control	Intervention

Intervention: Clinical Practice Guideline (CPG) on the management of routine oral examinations (ROE) and asymptomatic mandibular impacted third molars (MIM).

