## Intervention

### Implementation strategy

Participants in both trial arms receive a recently developed evidence-based CPG on ROE or MIM. The implementation strategy consists of one interactive IQual group meeting of approximately two to three hours with a minimum of eight GDPs each. These meetings discuss the selected intervention topic, and offer a more risk-based decision-making process guided by the CPG. Topics regarding risk management, such as identification of risk factors/indicators, preventive interventions, prognosis, monitoring, record keeping, and patient scheduling are presented. In addition, all participants receive feedback from personal and group characteristics retrieved from pre-test questionnaire and specific record forms, and are invited to make use of web-based patient risk vignettes for further individual training on risk assessment policy. These risk vignettes were developed by structured consensus procedures (modified Delphi) with expert groups consisted of acknowledged GDPs and oral surgeons in special fields. In addition, reminders (flow charts) and written patient leaflets with topical information are provided during the trial period. Flow charts comprise algorithms of decision-making aspects linked to the trial arm allocation. Depending on the allocated trial arm, participants are subjected to a set of planned interventions as described in Table 2.

**Table 2 T2:** Overview of planned interventions in groups I and II.

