**Randomisation**		

**Interventions trial arms**	**ROE group I**	**MIM group II**

Delivery CPG on ROE versus MIM by post	CPG ROE	CPG MIM
Education session IQual group	ROE education	MIM education
Online training website (individual feed back)	Access to ROE-based training	Access to MIM-based training
Reminder (flow chart), individual feed back record form Feed back by email	ROE- aspects Flow chart	MIM-aspects Flow chart
Registration in practice (25)	25 observations in practice chair side	25 observations in practice chair side
End trial	Questionnaire	Questionnaire

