### Sample size

The primary outcome measures in this study are collected from individual patients who are clustered within GDPs. GDPs are clustered within (existing) IQual groups which have been randomised to one of the two arms of the trial. The power calculation assumes that the primary outcomes are dichotomous measures, although some outcomes might be treated as continuous measures as well. On the basis of previous research and experience with IQual groups, we expect a relatively high clustering of scores within GDPs, for instance, the intra-cluster coefficient (ICC) for recall interval assignment was 0.29 [23], and a low clustering of scores within IQUAL groups (changing professional behaviour is largely determined by other factors). We use the ICC for clustering in IQual groups, because this was the unit of randomisation. We aim for a 20% change on primary outcomes (e.g. 20 to 40% patients receive individualised recall intervals). Assuming *a power of *80%, alpha = 0.05 and an effect size of 20% for both interventions and an estimated ICC of 0.03 based on previous estimates [21,22], the (Aberdeen) power calculation [24] revealed that six IQual groups (60 GDPs) should comprise 150 registrations (patients) per group, resulting in at least 450 registrations in each trial arm.

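### The hypothesis names guideline dissemination alone as comparator, but for each topic the control arm is sent no guideline on that topic, so added value over dissemination is not tested

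*Protocol article*

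**What the plan says.** - **Hypothesis.** The section Scientific hypothesis states that multifaceted implementation "is more effective and efficient compared to dissemination of CPGs only".
- **What is delivered.** The section Implementation strategy says: "Participants in both trial arms receive a recently developed evidence-based CPG on ROE or MIM". Table 2 has a row "Delivery CPG on ROE versus MIM by post", placed below the randomisation line, with the ROE guideline in the group I column and the MIM guideline in the group II column.
- **Who is the control.** The section Study design says: "Groups of GDPs allocated to either of these arms act as each other's control group". Table 1 marks each group as intervention for its own topic and control for the other, and its legend describes the intervention in terms of the guideline itself.
- **Overlap between the guidelines.** Study design says that in the ROE arm "the CPG only mentions the necessity of third molars screening in general as routine oral care", and assumes that the two topics are largely independent.
- **Background access.** The Background says that both guidelines "are available for educational purposes in clinical practice".

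**The concern.** A hypothesis of superiority over dissemination alone calls for a control arm that is sent the same guideline without the other components. The tables describe something else: the guideline goes only to the arm that also gets the meeting, feedback, web training and reminders on that topic.

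What is at stake is the conclusion. If the result favours the intervention, the hypothesis as worded invites the claim that the meeting, training and reminders add something to sending out a guideline. That is the claim of practical interest, because those components cost dentists' time, which the Costs section counts. The randomised comparison cannot support it. The same applies to the efficiency half of the hypothesis.

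**Working it through.** **Step 1. Exposure of each arm, by topic** (Tables 1 and 2 and the section Implementation strategy).

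| Component | ROE topic: group I | ROE topic: group II (control) | MIM topic: group II | MIM topic: group I (control) |
|---|---|---|---|---|
| Guideline on that topic, by post | yes | no delivery stated | yes | no delivery stated |
| Group meeting on that topic | yes | no | yes | no |
| Web training on that topic | yes | no | yes | no |
| Reminder flow chart and feedback on that topic's aspects | yes | no | yes | no |
| Registrations and questionnaires | yes | yes | yes | yes |

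No section sends the ROE guideline to the MIM arm or the MIM guideline to the ROE arm. Within each topic, the guideline row has the same pattern as the meeting, training and reminder rows.

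**Step 2. What the contrast estimates.** For one topic, let *D* be the effect of posting its guideline against usual practice, and *S* the further effect of the other components once the guideline has been posted. The arms differ by *D + S*. The hypothesis concerns *S*. With two arms there is one contrast and two unknowns, so *S* cannot be recovered. The allocation-by-time interaction in the Statistical analysis section also estimates *D + S*. No choice of model changes this, because it follows from what was sent to whom.

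**Step 3. Could the other topic's guideline stand in?** No. By the article's own account the ROE guideline treats third molars only in general terms, and the design relies on the topics being largely independent.

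**Step 4. Could background availability stand in?** Not as a controlled comparator. The Background states no delivery to control dentists, and Table 2 treats posting as an arm-specific step after randomisation. Some control dentists may have seen the guideline; the article does not say how many.

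**Step 5. Does the sample size settle which comparator was meant?** The inputs in the section Sample size are "80%, alpha = 0.05 and an effect size of 20% for both interventions", with the example "e.g. 20 to 40% patients receive individualised recall intervals", an intra-cluster coefficient of 0.03 and 150 registrations per group. Sidedness is not stated; two-sided is assumed.

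- Individually randomised size, normal approximation: n = [1.96·√(2 × 0.30 × 0.70) + 0.8416·√(0.20 × 0.80 + 0.40 × 0.60)]² / 0.20² = 81.2, so 82 per arm.
- Design effect: 1 + (150 − 1) × 0.03 = 5.47.
- Product: 82 × 5.47 = 448.5, so 449 per arm, against the stated 450. Power at 450 per arm is 80.5%.

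The figure reproduces. It does not bear on the comparator: the article does not tie the 20% starting level to dentists who have been posted a guideline.

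**The case against.** **The other side.** The phrase in the hypothesis could mean the dissemination that had already happened, since the Background says that the guidelines are available. It does not say that dissemination is a trial-delivered arm or a mailing. On that reading the fault is an undefined term. The randomisation, outcomes, model and sample size are untouched, and the estimate of package against control stays valid and interpretable.

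**What stands of it.** The estimate is indeed valid for its own contrast, and the fault lies in how the hypothesis labels the comparator. The background reading is possible but does not rescue the wording: availability is uncontrolled exposure of unknown extent, and posting the guideline remains part of what only the intervention arm receives on that topic. Even if some control dentists had the guideline, the contrast would still include the effect of the mailing.

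**Stronger readings a reader might infer, which the article does not support:**

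- *The control gets no guideline, or nothing at all.* It gets the other topic's guideline and does the same type of registrations and questionnaires. Implementation strategy also says that all participants receive feedback drawn from the pre-test questionnaire and record forms, although Table 2 makes the later feedback arm-specific.
- *The cost-effectiveness ratio is wrongly defined.* The Analysis section under Economic evaluation takes differences between the randomised arms for each topic. That is the comparator actually used; no ratio against dissemination alone is planned.
- *The aim is wrong.* The section Aim of the study names no dissemination-only comparator.
- *Mailing would explain a stated share, or all, of a positive result.* The article gives no mailing effect, so any such share would be an assumption.

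**Conclusion.** The hypothesis as worded does not match the randomised contrast. For each topic the trial tests guideline delivery plus meeting, feedback, web training and reminders against usual practice without a trial-delivered guideline on that topic. It does not test added value over dissemination alone. This rests on Tables 1 and 2 and the Implementation strategy text being a complete account of who is sent which guideline; nothing in the article indicates otherwise.

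The size of the discrepancy is *D*, the effect of posting the guideline, and it cannot be derived from the document. The fault is confined to the comparator in the hypothesis and to conclusions drawn from it. It does not invalidate the package-against-control estimate.

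**What to change.** Restate the hypothesis so that, for each topic, delivery of the guideline together with multifaceted implementation is compared with usual practice without a trial-delivered guideline on that topic. Limit the effectiveness and cost-effectiveness conclusions to that comparator, and claim no added value over dissemination alone. Leave the aim and the definition of the cost-effectiveness ratio as they are. The cost is a change of wording, with no new data and no change to design or analysis.

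Posting both guidelines to all groups would create a true dissemination-only control, but it is a design trade-off and not a simple repair. The Randomisation section reports allocation as already done, and the change would disturb the 20% to 40% planning assumption. As an illustration only: suppose such a control reached 25% or 30% (assumed; not in the article) against 40% under intervention. With 450 per arm and a design effect of 5.47, the effective size is 450 / 5.47 = 82.3 per arm, and power by the same approximation falls from 80.5% to about 54% or 27%. The sample size would have to be worked out again.

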## Methods

### Study design

The study is a cluster-randomised trial with incomplete block design. In one trial arm, the intervention focuses on individual decision-making in scheduling ROEs. In the second arm, the intervention focuses on monitoring and decision-making regarding prophylactic removal versus retention of MIM. Groups of GDPs allocated to either of these arms act as each other's control group. To reduce potential contamination, groups of GDPs are randomised rather than individual GDPs (Table 1). We assumed that the two clinical conditions (or practices) were largely independent of one another, i.e. performing one would not necessarily influence the other. In the ROE arm, the CPG only mentions the necessity of third molars screening in general as routine oral care. In the MIM arm, the CPG provides an extensive, but specific, decision-making algorithm, i.e. how to deal with mandibular asymptomatic impacted third molars.

**Table 1 T1:** Balanced incomplete block design

**Intervention**	**CPG**	
	**ROE**	**MIM**

Group I (ROE)	Intervention	Control
Group II (MIM)	Control	Intervention

Intervention: Clinical Practice Guideline (CPG) on the management of routine oral examinations (ROE) and asymptomatic mandibular impacted third molars (MIM).

### Recruitment of GDPs and inclusion/exclusion criteria

Dental peer groups ("IQual-group"), each comprising at least eight participating GDPs, are the unit of randomisation. An IQual group consists of GDPs who attend monthly sessions scheduled for discussion on practice-related topics as part of a quality assurance program. Participants in peer groups generally support quality-improvement procedures, and are experienced in continuing dental education and professional cooperation. The Dutch Dental Association (NMT) has initiated this system, and supports nationwide dental peer groups extensively, e.g., offering professional support, feedback and continuing education programmes. All IQual-groups were invited to participate in this study by a general announcement on the NMT website, dependent on their ability to begin the study within two to three months. Those groups that were interested in participating were invited to visit a section of the NMT website  for members only that provided more detailed information on the project.

### GDP inclusion criteria

The inclusion criteria consisted of:

• GDPs who work for at least for three days a week in general dental practice for a minimum of three years

• GDPs who have a patient population of regular ROE-attendees and manage their patient records electronically.

• GDPs were required to give their informed consent for the assessment and evaluation of electronic patient records. Patient data are collected anonymously.

### Patient's inclusion criteria

To be eligible for inclusion in the study, all patients must have regularly visited the same dentist at least once a year for ROEs over the preceding three years. For the MIM arm, patients should also be between 17 and 35 years of age, and with disease-free impacted mandibular third molars in retention.

### Patient's exclusion criteria

For the ROE arm, patients with symptomatic-driven (emergency) attendance in dental practice, or regular attendance in the participating dental practice of less than three years, are excluded from the study. For the MIM arm, patients with symptomatic or previously removed third molars, or regular attendance in the participating dental practice of less than three years, are excluded from the study

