### Outcomes and instruments

#### ROE study

Table 3 lists the outcome parameters and instruments used. For the ROE arm, the primary outcome measure is the use and appropriateness of individualised risk assessment measured through the assigned recall intervals (in months). The appropriateness will be assessed as follows:

**Table 3 T3:** Outcome parameters and instruments

**Outcome parameter**		**Instruments**
**Primary ROE-outcomes**	Clinical Performance/decision-making: Number of patients per GDP with assigned recall interval (months) based on individual risk profile assessment. For high-risk children and adolescents' intervals less than seven months, in case of low risk profile more than seven months; for low-risk adults' profiles, nine months equal or more, and for high-risk adults' profiles less than nine months.	**Patient record, registration form, to analyse risk management**
**Secondary ROE-outcomes**	Clinical Performance/decision-making: Number of patients per GDP with prescribed individual frequency of BWs (months). For high-risk children and adolescents, frequencies of less than 24 months, and for low-risk profiles, frequencies of more than 36 months; for high-risk adults, prescription frequencies less than 36 months, and for low risk adults, prescription of more than 48 months. Number of patients per GDP with periodontal DPSI-score > 1, and prevalent caries, who have been given feedback, information and preventive advice, registered in patient record or registration form. Efficacy data/cost-effectiveness scores: Mean overall length in months of recall intervals per GDP over the past 3 yrs Mean total number of BW(s) and other radiographs over past 3 years Type of performer GDP/Oral hygienist/others (level of graduation, education) Total number of additional interventions performed during ROE (polishing, removal of calculus: coded as M50, M55). Professional attitudes and compliance: Measured at the beginning and end of the trial, by questionnaire.	**Patient record, registration form, questionnaire to analyse additional performance and cost-analysis**
**Primary MIM-outcome**	Clinical performance/decision-making: Number of patients (between 17 -35 yr of age) with removed versus retained MIMs in accordance with CPG, or with indication for removal. Number of risk-based assessment radiographs between 17– 35-yrs/per patient with risk-based for assessment of prognosis MIM.	**Patient record, registration form to analyse risk management**

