#### MIM study

For the MIM arm, the primary outcome is the use and appropriateness of individualised MIM risk management. The appropriateness will be assessed as follows:

• Patients (17–35 years of age) with removed versus retained MIMs over the past five years as a proportion of patients aged between 17–35 years of age per practice

• Radiographs used for monitoring patients mentioned above to perform a risk-based assessment and prognosis of MIM over the past five years.

A secondary outcome measure is GDPs- attitudes and compliance concerning the recommendations of the MIM-CPG, and relating that information to patients. This measure will use data from patient interviews to confirm risk-based performance.

All data will be collected using special registration forms to be completed by GDPs and patient records available in practices. Questionnaires, patients' records, and registration forms will provide information to assess all outcome parameters. The structured registration forms were used in a previous self-recording study [23].

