### Data collection

After their informed consent to participate, GDPs will be invited to first complete a questionnaire to collect personal and practice characteristics, as well as aspects of attitude and compliance. Individual assessment of electronic patient records with regard to the outcome measures, combined with a special registration form (to be applied individually in daily practice), will be used during the evaluation period.

Baseline information will be collected before randomisation of groups, as well as at the end of the trial after seven to nine months. Each GDP will be instructed to complete at least 20 forms per registration period. As each peer group consists of at least eight participants, and each arm will consist of three groups, this will result in a minimum of 480 registrations per trial arm. Finally, questionnaires will be collected from GDPs, dentist's assistants and co-workers to assess acceptance and applicability.

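### The MIM eligibility criteria exclude the past removals that the MIM primary outcome counts, that outcome has two definitions, and the criteria are written per arm although each arm is the control for the other topic

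*Protocol article*

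**What the plan says.** All references are to the protocol article.

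- **Patient's inclusion criteria:** the MIM condition reads "For the MIM arm, patients should also be between 17 and 35 years of age, and with disease-free impacted mandibular third molars in retention". It comes on top of a general requirement of regular attendance.
- **Patient's exclusion criteria:** the MIM sentence begins "For the MIM arm, patients with symptomatic or previously removed third molars" and excludes these patients from the study. The ROE topic has its own sentence, beginning "For the ROE arm, patients with symptomatic-driven (emergency) attendance in dental practice", with no condition on age or third molars.
- **MIM study (text definition of the primary outcome):** the count is of 17- to 35-year-olds "with removed versus retained MIMs over the past five years as a proportion of patients aged", with the same age range as denominator in each practice. Radiographs over the same five years are a second component.
- **Table 3 (same primary outcome):** the count is of patients "with removed versus retained MIMs in accordance with CPG, or with indication for removal". No look-back period is given.
- **Study design:** the two arms serve as mutual controls, in the sentence that begins "Groups of GDPs allocated to either of these arms act as each". Table 1 shows both topics compared across both groups.
- **Data collection:** baseline is collected before randomisation, and each GDP completes at least 20 forms per period. On eight GDPs per group and three groups per arm, the article concludes that "this will result in a minimum of 480 registrations per trial arm". Table 2 gives 25 observations per GDP and places the first set above the randomisation row.

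**The concern.** Three things do not fit together.

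1. The criteria select on the outcome. A patient must still have the molar, and a removal disqualifies the patient, but the text definition counts removals over the preceding five years. A site following the criteria would leave out the past removals that the outcome needs.
2. The text gives a removal share with a five-year window. Table 3 gives agreement with the guideline with no window. These are different quantities: a removal that the guideline supports is a success under Table 3 but merely a removal under the text.
3. The criteria are attached to arms, whereas the design needs each topic measured on comparable patients in both arms. If the criteria differ by randomised arm, the comparison on each topic mixes the intervention effect with differences in age and case mix.

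At stake are the meaning of one of the two primary outcomes and the comparability of the control data. Both depend on who is registered, so they must be settled before the forms are filled in.

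**Working it through.** **1. Criteria against the text outcome.** Inclusion requires molars "with disease-free impacted mandibular third molars in retention", and exclusion removes those previously removed. At inclusion, the number of past removals among admitted patients is therefore 0. The five-year look-back can return only retained molars from these patients.

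What happens after inclusion depends on whether the same patients are followed. The article does not say that they are. It asks for a set of forms in each registration period and says that patient data are collected anonymously.
- Same patients followed: a molar retained at baseline can be counted if it is later removed.
- Fresh sample under the same criteria: a patient whose molar was removed after baseline counts as previously removed and is excluded again.

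**2. Text against Table 3.**

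| | MIM study text | Table 3 |
|---|---|---|
| Counted | removed versus retained | removed versus retained as the guideline advises, or indication for removal |
| Denominator | patients aged 17–35 per practice | not stated beyond age 17–35 |
| Window | past five years | none |

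**3. Arm against topic.** The ROE outcome covers ages 0 to 18 and adults, with different thresholds. If arm means the randomised arm, MIM-arm patients are all 17 to 35, so they cannot be ROE controls for children under 17 or adults over 35. ROE-arm patients need not have an impacted molar. At baseline the arm is not yet known, so criteria by randomised arm could not be applied then.

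**4. Sample size.** Inputs from the Sample size section: 20% versus 40%, alpha 0.05 (taken as two-sided), power 80%, ICC 0.03, 150 registrations per group, three groups per arm.

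Individually randomised size, normal approximation without continuity correction:

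n = [1.96·√(2·0.3·0.7) + 0.842·√(0.2·0.8 + 0.4·0.6)]² / 0.2² = (1.270 + 0.532)² / 0.04 ≈ 81.2, rounded up to 82 per arm.

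Design effect = 1 + (150 − 1)·0.03 = 5.47, and 82 × 5.47 = 448.5. The stated 450 per arm reproduces.

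The article describes one set of forms and does not say how many serve each topic. An even split is an assumption, shown for two counts:
- Minimum count: 8 GDPs × 3 groups × 20 forms = 480 per arm, so 240 per topic (80 per group).
- Larger count: 60 GDPs give 30 per arm; 30 × 25 observations = 750, so 375 per topic (125 per group).

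Power = Φ[(0.2·√n_eff − 1.96·√0.42) / √0.40], where n_eff = registrations per arm ÷ design effect:

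| Per arm, per topic | Per group | Design effect | n_eff | Power |
|---|---|---|---|---|
| 450 | 150 | 5.47 | 82.3 | 80.5% |
| 375 | 125 | 4.72 | 79.4 | 79.1% |
| 240 | 80 | 3.37 | 71.2 | 74.5% |

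The loss is small because clustering by group dominates. These figures keep the protocol's own method and inputs. The 20% and 40% are its recall-interval example; no MIM rate is given.

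**The case against.** The strongest reply is that arm here means topic. The ROE study and MIM study sections define each topic's outcome for an arm, although each outcome must be measured in both groups. Baseline before randomisation makes selection by randomised arm impossible at that point. This reading is plausible, and under it the case-mix problem disappears. It stands as a reason not to claim confounding as a fact. It does not close the point, because no section states it and the first two contradictions remain.

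A second reply is that removals are not lost. Previously removed describes status at inclusion, Table 3 also counts an indication for removal, the radiograph component is unaffected, and the text denominator is per practice, which could mean a count from practice records. Part of this stands: the outcome is not empty under every reading. But a practice-wide count overrides the stated exclusion from the study, and counting later removals needs follow-up of the same patients, which is not described.

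A reader might go further and infer that there can be no removed cases at all, or that each arm has no usable controls. The documents support neither. Only removals before inclusion are excluded with certainty. The ROE criteria have no age limit, so ROE-arm patients may include 17- to 35-year-olds with impacted molars, and MIM-arm patients can be ROE controls within that age range. Nor do the documents give the share of ROE-arm registrations that would meet the MIM criteria, so no count of such controls can be derived.

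Finally, an article may leave form quotas to the full protocol. That is fair for the quotas alone, but not for criteria and outcome definitions that contradict each other where they are stated.

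**Conclusion.** The contradiction stands. As written, the MIM criteria keep past removals out of a primary outcome defined by a five-year look-back on removals, and keep out removals since baseline as well if the second registration is a fresh sample. The text and Table 3 define that outcome differently. The comparability problem is conditional: it arises if arm means the randomised arm, and the article neither states nor excludes that.

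The weight lies on validity. The sample size arithmetic is sound on its own terms, and even the smaller even split costs about six percentage points of power (80.5% to 74.5%). The split is an assumption, and a patient eligible for both topics could serve both, although the article does not say so. The inconsistency should be corrected before registration because it changes which patients are recorded, which analysis cannot repair.

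**What to change.** - State eligibility per topic, and apply each set identically in both arms and both registration periods.
- For MIM, include 17- to 35-year-olds with an asymptomatic impacted mandibular third molar present at the start of the measurement window, and do not exclude removals that occur within that window.
- Use one MIM outcome definition, one denominator and one window, in the same words in the MIM study section and in Table 3.
- Say how many registrations per GDP serve each topic, and whether one patient can serve both. If they are split, restate the power for the resulting number per topic; extra forms are not needed for this point.

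The cost is rewording the criteria, the outcome definition and the registration form instructions. No new procedure and no additional registrations are required.
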